### Measures

In general, we aim to examine the effectiveness of our modified secondary distribution models. Primary outcomes of this trial are the number of alters, first-time testing alters, and HIV-positive alters in each arm, therefore, all testers’ information will be specifically clarified and recorded. All data will be collected through JINSHUJU, a secure online platform where participants can apply for HIVST kits, report testing results, and complete the baseline and follow-up questionnaires. All data collected from participants will be examined and deduplicated according to phone number and IP.

In the baseline survey, we will collect the socio-demographic characteristics, sexual orientation, sexual behavior, HIV testing history, and social network. When alters return the results, they will also complete a questionnaire online. In this survey, except for basic information on socio-demographic characteristics, sexual orientation, sexual behavior, HIV testing history, and social network will be collected. We will also investigate the attitudes and experiences towards self-test. The follow-up survey for indexes will take place 3 months after the application completed, which focuses on experiences and attitudes on using and distributing self-test kits. The survey mainly inquires about the occurrence of intimate partner violence (IPV) or other adverse events, the relationship between the indexes and the alters, whether indexes have tested together with the alters, and whether indexes have guided the alters on how to perform HIVST.

Specifically, in our surveys, socio-demographic characteristics include indexes’ age, sex, marital status, the highest level of education completed, and monthly income level. Sexual behavior within 3 months includes previous sex with males and females, role during sex with males, condom use, number of sex partners, and drug use. HIV testing history includes health care facility-based and online HIV testing experience. Social network collects community engagements [7], community connectedness [20], identity fusion [21], and social cohesion [22].

All blood samples will be analyzed using *SD Bioline* HIV/Syphilis duo test kits (*SD Bioline Company*, South Korea). Participants will collect fingertip blood samples by themselves according to the instruction. The trained staff of the CDC or CBO will check and read the photos of result and record them in JINSHUJU. The results are subject to the reading of the staff.

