#### Secondary analysis

Results of the follow-up survey for indexes and the survey for alters will be used for measuring secondary outcomes, i.e. risky sexual behavior, adverse events during secondary distribution, and experience and attitude towards HIV testing. High-risk sexual behavior, defined as unprotected sex, substance use, or multiple sexual partners, are determined from survey questions such as “How often do you wear a condom during anal sex?”, “In the past three months, how many sexual partners did you have?”, “In the past three months, have you used drugs before sex?”, etc. Adverse events or IPV that happened on alters during distribution are determined from the question “Have you experienced any of the following IPV when received the HIVST kit from the index?”. Alters’ experience and perception of HIVST are determined from total 20 question items, e.g. “How difficult do you feel about completing HIV self-testing?”, “How many men did you have anal sex with after HIV self-testing?”, “Which testing do you prefer, facility-based testing or HIV self-testing?”, etc. We will use chi-square tests to compare each outcome of interests between SD/monetary incentives group and control group, SD/monetary incentives and peer referral group and control group, and also between two intervention arms.

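### Chi-square is fixed for every secondary outcome, although some of the alter experience and perception items named are graded or counts; on those items the plan gives up power that a rank, trend or count method would usually keep.

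*Protocol article*

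**What the plan says.** The protocol's Secondary analysis names one method for the secondary outcomes: "We will use chi-square tests to compare each outcome of interests between SD/monetary incentives group and control group". The sentence goes on to cover the combined arm against control and the two intervention arms against each other. No other test is named for these outcomes.

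The same section describes what will be compared:

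- Risk behaviour is given by category: "High-risk sexual behavior, defined as unprotected sex, substance use, or multiple sexual partners". It is derived from questions such as "How often do you wear a condom during anal sex" and "In the past three months, how many sexual partners did you have".
- "Alters’ experience and perception of HIVST are determined from total 20 question items". The examples include a graded question ("How difficult do you feel about completing HIV self-testing"), a count ("How many men did you have anal sex with after HIV self-testing") and a nominal question on preferred type of test. No grouping or cut-point is given for any of them.

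Elsewhere the protocol does separate kinds of variable. The Primary analysis uses a t-test for means and chi-square for proportions, and the Data analysis section summarises numerical baseline variables by mean and standard deviation.

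**The concern.** A chi-square test needs categories. For a graded answer or a count there are two plain ways to apply the Pearson version. One keeps all the categories and treats them as unordered, so that a step from very easy to easy counts the same as a step from very easy to very difficult. The other cuts the answers into two groups, at a point the protocol does not state. The first ignores order; the second ignores everything except which side of the cut an answer falls on.

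At stake is the chance of detecting a real difference between arms in how alters found self-testing, or in their reported number of partners afterwards. An overall chi-square on several categories also supplies no single effect estimate. The protocol states this choice of test outright, so it is not merely a detail left to a fuller plan.

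**Working it through.** The protocol gives no power figure for secondary outcomes; its Sample size section concerns alters per index. There is therefore no figure to reproduce, and the check asks how much power the stated test gives up.

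**Inputs from the protocol.** 100 indexes per arm with loss of 0.20: 100 × (1 − 0.20) = 80 per arm. Expected alters per 100 indexes, from means of 0.65, 1.0 and 1.4: 65, 100 and 140.

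**Assumptions (not in the protocol).** Five-level item, two-sided 0.05, no clustering of alters within index. Example control distribution 10/20/30/25/15%; proportional odds ratio 2.0.

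**Step 1, shifted distribution.** Control cumulative proportions 0.10, 0.30, 0.60, 0.85 have odds 0.111, 0.429, 1.50, 5.67. Halving these gives 0.056, 0.214, 0.75, 2.83, that is, cumulative proportions 0.053, 0.176, 0.429, 0.739. The shifted distribution is 5.3/12.4/25.2/31.1/26.1%.

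**Step 2, unordered chi-square (4 df).** Noncentrality = n Σ (p0 − p1)²/(p0 + p1) = 80 × 0.0732 = 5.86. Against the critical value 9.49, power is 0.46 (simulated: 0.45).

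**Step 3, chi-square after a cut.** Power = Φ[(d − 1.96·s0)/s1], where d is the difference in proportions, s0 = √(2p̄(1 − p̄)/n) and s1 = √((p0(1 − p0) + p1(1 − p1))/n).

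- Cut after level 3 (0.60 vs 0.429): (0.1714 − 1.96 × 0.0790)/0.0779 = 0.21, power 0.58 (simulated: 0.57).
- Cut after level 4 (0.85 vs 0.739): (0.1109 − 1.96 × 0.0639)/0.0633 = −0.23, power 0.41 (simulated: 0.41).
- Cut after level 1 (0.10 vs 0.053): (0.0474 − 1.96 × 0.0420)/0.0418 = −0.83, power 0.20.

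**Step 4, rank test.** Proportional-odds approximation: power = Φ[ln(2.0) × √(n(1 − Σp̄³)/6) − 1.96] = Φ[0.693 × √(80 × 0.944/6) − 1.96] = Φ(0.50) = 0.69 (simulated: 0.67).

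**Step 5, other assumed five-level distributions, 80 per arm, odds ratio 2.0.** Simulated power was 0.41-0.47 unordered, 0.19-0.58 after a cut and 0.63-0.69 for rank-sum. Simulated type I error was about 5% for every method.

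**Step 6, alter numbers implied by the Sample size section.**

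| Alters | Rank-sum | Unordered | Cut |
|---|---|---|---|
| 65 vs 100 | 0.64-0.67 | 0.43-0.46 | 0.25-0.58 |
| 65 vs 140 | 0.70-0.75 | 0.51-0.54 | 0.26-0.63 |

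**Step 7, a count.** Negative binomial, mean 2.0 vs 1.3, dispersion 1.5, 80 per arm: rank-sum 0.57, two-or-more by chi-square 0.44, unordered chi-square on 0 to 6+ 0.33.

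**Step 8, a pattern less kind to the rank test.** Moving only one threshold (odds ratio 2.25, 80 per arm), chi-square cut at exactly that threshold beat rank-sum in all six cases tried, for example 0.61 vs 0.43 and 0.73 vs 0.65. The advantage turns round if the cut is placed elsewhere.

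**The case against.** Four arguments on the other side carry weight.

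- **Questions are not outcomes.** A reader might infer that all the secondary outcomes are mis-tested, condom use and partner number included. The protocol does not support that. It defines high-risk behaviour through categories and uses those questions to derive them, and chi-square fits the result. Partner violence, drug use and test preference are categorical too. This stands, and it confines the point mainly to the graded and count items among the 20 alter questions, an unknown share of them.
- **A linear-trend test is also a chi-square test.** It uses order and performs much like a rank test (simulated power 0.60-0.69 against 0.62-0.69). The wording does not exclude it, but an unqualified chi-square is most plainly read as Pearson's, so naming the test is worthwhile.
- **The size rests on a proportional shift.** This stands: Step 8 shows the ranking can reverse. However, that needs a cut at the right threshold, and the protocol states no cut. Response formats are also unseen, and a count may be asked in bands.
- **Detail may be left to a fuller plan.** Cut-points and item coding may be. The choice of one test for each outcome is already made here.

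Other stronger readings also fail. The test is not invalid, since type I error holds. A two-by-two table does show direction. The protocol gives no figure suggesting that high-risk behaviour is too common to change, and it nowhere says that a null result would be taken as no change.

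**Conclusion.** The point holds as a cheap improvement of minor severity. For the graded and count items that the Secondary analysis itself names, Pearson chi-square is usually the less efficient choice. In the worked example it costs about 22 points of power when categories are unordered (0.67 against 0.45) and about 10 even at the best cut (0.67 against 0.57); in the count example the losses are 24 points unordered (0.57 against 0.33) and 13 after the cut (0.57 against 0.44). These figures rest on assumed layouts, distributions and effects, a shift spread across the levels, and independent alters. They show the likely direction and rough size and do not predict this trial's power. The primary outcomes are untouched, and so is the use of chi-square for yes/no and nominal secondary outcomes.

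**What to change.** In the Secondary analysis, replace the single-test sentence with a rule by type of item:

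- **Yes/no and nominal outcomes** (high-risk behaviour as defined, any partner violence, drug use before sex, preferred test): keep chi-square.
- **Graded items** (difficulty of self-testing and other ordered answers): rank-sum test, linear-trend test or proportional-odds model.
- **Counts** (men after self-testing): rank-sum test or negative binomial model.
- **Condom frequency and number of partners**: report on their recorded scale, by the graded and count rules respectively, alongside the defined high-risk categories. The Measures section already lists both among the data collected.

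State any cut-point in advance, and give an effect estimate with a 95% confidence interval for each of the three arm comparisons.

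The cost is one paragraph, with no new data or participants. Trial status says that statistical analysis has not begun, so the rule can still be fixed in advance. The one drawback is that odds and rate ratios are slightly harder to explain than percentages, which can still be tabulated.

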### Outcomes

The primary outcomes of this trial consist of three parts: 1) Mean number of motivated alters who have photo-verified self-testing per index in each arm; 2) Proportion of first-time HIV testing among alters in each arm; 3) Proportion of alters with a positive HIV testing result in each arm.

The secondary outcomes of this study consist of three parts 1) Risky sexual behavior among indexes and alters in each arm; 2) Adverse events reported during secondary distribution among indexes and alters in each arm; 3) Attitude towards and past experiences of HIVST and sexual behavior among alters in each arm.

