### Sample size

According to preliminary study results, on average, the number of alters motivated by an index man was 0.65 through standard secondary distribution, 1.0 through SD/monetary incentives intervention, and 1.4 through SD/monetary incentives plus peer referral intervention. We assumed that the variances of the three groups were equal with the same standard deviation of 0.5 (preliminary data, unpublished results). Further, we estimated an effective sample size of 300 participants (100 in each group), with a power of 0.90, an alpha of 0.05, and a lost to follow-up rate of 0.20.

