This study generates a social innovation and policy implication that expands and improves the public service of HIV prevention and control, with the use of social network strategies. From the perspective of digital health, digital network-based secondary distribution of HIVST is an innovative delivery approach that can reach hidden MSM. Beyond the geographical limitation, some MSM, especially those in remote conservative areas, have limited access to facility-based services, while digital platforms might motivate them to perform HIV testing. Furthermore, by taking advantage of digital network-based distribution, we aim to reduce fear of stigma associated with conventional HIV testing services in healthcare facilities. Social network strategies, especially peer referral, taps into self-identity with a community and trust to provide services more effectively. Empowering vulnerable individuals within a community by offering essential resources has both research and policy implementations for expansion of HIV services in other hard-to-reach populations. Upon completion of the study, we will provide the community with practical digital network-based HIVST interventions and scientific evidence on the feasibility and acceptability of the secondary distribution approaches. In addition, practical experience and knowledge gained from conducting the interventions can be considered and applied to further trials in enhancing HIV testing. If successful, the strategy has the potential to be implemented in similar regions.

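### Adverse events and IPV are compared between arms only by chi-square tests, which at this trial's size would usually miss a doubling of an uncommon harm and would not show how much excess harm remains possible

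*Protocol article*

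**What the plan says.** Under Outcomes, the second secondary outcome is "Adverse events reported during secondary distribution among indexes and alters in each arm". It is the only outcome labelled as harm. Under Measures, indexes are asked about IPV and other adverse events in the 3-month follow-up survey. Under Secondary analysis, harm to alters is taken from a survey question on IPV at the time the kit was received.

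The analysis of all secondary outcomes is then fixed in one sentence: "We will use chi-square tests to compare each outcome of interests between SD/monetary incentives group and control group". The same sentence extends the test to the peer-referral arm against control and to the two intervention arms against each other. It names no estimate of effect, no interval and no separate treatment of harm.

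The Sample size section rests on the mean number of alters alone: "the number of alters motivated by an index man was 0.65 through standard secondary distribution", then "1.0 through SD/monetary incentives intervention, and 1.4 through SD/monetary incentives plus peer referral intervention". No adverse event or IPV rate appears anywhere in the article.

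**The concern.** A test suited to attitudes and risk behaviours is applied unchanged to an outcome where events are likely to be few. Three things go wrong together.

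- **Low power.** With uncommon events and about 65 to 140 people per arm, a non-significant result is the likely one even if harm has doubled.
- **Poor fit to the data.** The Pearson chi-square is unreliable when expected counts are very small. It also assumes independent observations, whereas one index may pass on up to five kits and, in the peer-referral arm, share a link with up to five more people.
- **Uninformative output.** A p-value does not tell the reader how large an excess of harm the data still allow.

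This matters because both intervention arms pay the index for each alter who returns a result, which could plausibly put pressure on partners. The Discussion looks towards wider use: "If successful, the strategy has the potential to be implemented in similar regions". That sentence does not mention harm, but anyone acting on it would want to know how much excess IPV the trial can exclude.

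**Working it through.** **1. The plan's own size.** The article states: "we estimated an effective sample size of 300 participants (100 in each group), with a power of 0.90, an alpha of 0.05", with 20% loss to follow-up and "the variances of the three groups were equal with the same standard deviation of 0.5". The smallest pairwise difference in means is 1.0 − 0.65 = 0.35. At two-sided 5% and 90% power:

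n per arm = 2 × (1.960 + 1.282)² × 0.5² / 0.35² = 42.9, so 43.

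Allowing for 20% loss, 43 / 0.8 = 53.75, so 54 per arm and 162 in total. The stated 300 does not reproduce; it is larger than its inputs require. That has no bearing on this point, except to confirm that the size was set for alters per index and not for harm.

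**2. Numbers available for harm** (from Sample size)
- Alters, from 100 indexes per arm: 0.65 × 100 = 65 (control), 1.0 × 100 = 100 (incentives), 1.4 × 100 = 140 (incentives plus referral).
- Indexes: 100 per arm, or 100 × 0.8 = 80 after the stated loss.

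**3. Probability of missing a doubling.** The control rates of 2%, 5% and 10% are assumptions. The test is the uncorrected Pearson chi-square at two-sided 5%. The miss rate is the exact binomial probability, summed over all 2 × 2 tables with |z| ≤ 1.96, where z = (p̂₁ − p̂₂) / √[p̄(1 − p̄)(1/n₁ + 1/n₂)] and p̄ is the pooled proportion. Observations are taken as independent.

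| Comparison | 2% to 4% | 5% to 10% | 10% to 20% |
|---|---|---|---|
| Alters, incentives v control (100 v 65) | 93% | 80% | 59% |
| Alters, referral v control (140 v 65) | 94% | 80% | 57% |
| Alters, between intervention arms (140 v 100) | 90% | 72% | 43% |
| Indexes, 80 v 80 | 90% | 79% | 58% |
| Indexes, 100 v 100 | 89% | 73% | 48% |

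A check by hand for 65 v 100 at 5% to 10%:
- p̄ = (3.25 + 10) / 165 = 0.0803.
- Standard error under no difference = √[0.0803 × 0.9197 × (1/65 + 1/100)] = 0.0433.
- Standard error under the alternative = √[0.05 × 0.95/65 + 0.10 × 0.90/100] = 0.0404.
- (0.05 − 1.96 × 0.0433) / 0.0404 = −0.86, so power is about 0.19 and the miss rate about 81%, against 80% exactly.

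**4. Sensitivity**
- If the 20% loss also applies to alters (52, 80 and 112), the miss rate for a doubling against control runs from 66% to 97% over the same base rates.
- Outside the assumed range, with no loss of alters and over all three alter pairs, it is 97% to 99% at a base rate of 1% and 8% to 21% at 20%.
- A tripling among alters against control is missed in 79% to 81% (2% to 6%), 43% to 47% (5% to 15%) and 8% to 10% (10% to 30%).

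**5. Expected counts.** At 2% versus 4%, the expected number of control alters with an event under no difference is (1.3 + 4.0) × 65/165 = 2.1 against incentives, and (1.3 + 5.6) × 65/205 = 2.2 against referral. Both are below the usual minimum of 5.

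**6. What an interval would add.** With no events at all, the exact two-sided 95% upper limit is 1 − 0.025^(1/n): 5.5% for 65 alters, 3.6% for 100 and 2.6% for 140. If two arms have none, there is no p-value of any use, yet these limits remain informative.

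**The case against.** The strongest reply is that the protocol contains no rule for inferring safety. Its hypotheses concern kits distributed, and its Discussion promises evidence on feasibility and acceptability. This stands. A reader might infer from the chi-square plan that a non-significant result will be presented as evidence of safety; no sentence says so, and the point here does not depend on it.

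A second reply is that naming a test does not rule out reporting counts and intervals, and that a condensed article may leave these to an analysis plan that is not shown. This stands in part. The absence of a margin is not a fault in a secondary outcome of a trial not sized for harm. But the article does fix a method for this outcome, and it suits sparse, clustered events poorly; that is a stated choice, not a missing detail.

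A third reply concerns size. The miss rates depend on assumed base rates and are not a property of the document. The lowest figure, 43%, belongs to the comparison of the two intervention arms, both of which pay, so it does not test whether payment raises harm. It would also be tempting to say that the test would very likely miss even a tripling. The calculations support that only at a control rate of 2%; at 5% a tripling is detected slightly more often than not, and at 10% nearly always. All of this is accepted.

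Finally, the 140 may be too many. The IPV item asks about receiving the kit from the index, and some alters in the referral arm order their own through a link, so the item may not fit them. Fewer exposed alters would leave less information.

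**Conclusion.** The concern holds in a limited form. The only between-arm method named for adverse events and IPV is a pairwise chi-square test, applied to an outcome for which the trial was not sized. Against control, at assumed control rates of 2% to 10%, a doubling among alters is missed in about 57% to 94% of trials; with 80 indexes per arm the range is 58% to 90%. These figures assume a two-sided 5% level, independent alters, no loss of alters, and all 140 referral-arm alters able to report an event. Loss raises them, and positive correlation among alters of one index would leave less information. The documents do not support reading the plan as a declared safety rule, nor any single miss rate as fixed by the design. What they support is that a better method for this outcome is available at little cost, and that Trial status says the analysis had not begun, so the change could still be specified in advance.

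**What to change.** In Secondary analysis, for adverse events and IPV only, replace the chi-square comparison with the following, separately for indexes and alters:

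- the number and proportion with an event in each arm, with exact 95% confidence intervals and the denominator stated;
- for each arm pair, the risk difference with a 95% interval suited to small counts, such as Newcombe or Miettinen-Nurminen; for alters, index-level resampling if there are enough events, so that alters sharing an index are not treated as independent;
- a sentence that a non-significant difference will not be reported as absence of harm.

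No formal non-inferiority margin is needed. Chi-square tests may stay for the other secondary outcomes as far as this point goes. The cost is a short change of wording and a few lines of code, with no new data or participants. The downside is that the safety statement will probably read as inconclusive, which is what a trial of this size can support.
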